#### Neurological Examination and Clinical Rating Scales

We will record the following patient demographics: age, sex, occupation, level of education, ethnicity, languages spoken, handedness, and pre-morbid medical history. We will document the mechanism of injury, severity illness score [SOFA and MODS (26, 27)] injury severity scale (for trauma patients), CT scan and/or MRI findings, clinical EEG/evoked potential findings, the magnitude of intracranial pressure (if monitored, and presence and duration of increased intracranial pressure), sedation/analgesia drug dose equivalents, delirium duration, ICU length of stay, and hospital length of stay. At each imaging time point, we will capture bedside clinical examinations of consciousness using the Glasgow Coma Scale (28), Full Outline of UnResponsiveness Score (FOUR Score) (29), and where feasible, the Coma Recovery Scale-Revised (CRS-R) (30). This will be done immediately before or after imaging occurs.

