### Statistical Analysis

To establish whether fMRI can aid prognostication in acute disorders of consciousness, imaging results will be related to long term behavioral and cognitive follow up assessments. For the somatosensory and auditory processing task, the Spearman's rank-order correlation coefficient will be used to measure the rank correlation between the extent of acute sensory processing and a patient's behavioral scores at 3-, 6-, and 12-months post- injury, as indexed by the GOS-E. This same method will be used to evaluate the relationship between the degree of acute functional connectivity, as measured by the correlation value to healthy controls, to long term outcome. For the movie narrative, the correlation between individual patients and the healthy control group during the intact clip will be related to long term outcome. The primary outcome will be 12 months post injury, and the secondary outcomes will be at 3 and 6 months. Linear regressions will be performed to investigate the effect of clinical and demographic variables on acute imaging features and patient outcomes. All statistical tests will be corrected for multiple comparisons using a False Discovery Rate. We will also determine the sensitivity, specificity, positive predictive value, and negative predictive value for the imaging procedures outlined in the protocol.

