Receiver operating characteristic (ROC) and area under the curve (AUC) analyses will be generated to identify a cut-off value differentiating conscious from unconscious patients, as well as patients who are to have a good or poor outcome for each paradigm. Outcome predictors (as assessed by the area under a receiver operating characteristic curve) will be compared between acute neuroimaging findings and traditional prognostic markers (such as EEG reactivity, pupillary reflexes, brainstem reflexes, serum biomarkers, evoked potential results) to assess whether functional neuroimaging responses are more accurate. We will account for patient's age, gender, days since injury, down time (for cardiac arrest patients), MODS and SOFA score, as covariates during the statistical analyses. Where possible, patients will be grouped by etiology in the statistical analyses. In line with the previous investigational neuroimaging literature, we will characterize a “good” outcome as a recovery that allows for sufficient function for independent activities of daily life (3, 18, 44), whereas a “poor” outcome will be defined as a severe disability that impacts all aspects of daily living, a coma, vegetative state/unresponsive wakefulness syndrome, and death. In respect to the GOS-E, a “good” outcome is characterized as a score of 4 or greater, signifying the ability to be left alone for up to 8 h during the day without assistance (8).

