## Discussion

This research protocol outlines a comprehensive neuroimaging program that aims to improve the diagnosis and prognosis of critically ill patients with a primary brain injury. Functional neuroimaging techniques will be used to (1) identify prognostic markers of good neurologic recovery, (2) develop reliable diagnostic tools for detecting consciousness, and (3) communicate with select patients who show signs of covert awareness. Long term recovery will be tracked using neurocognitive and behavioral tests, and imaging results will be related to these outcome measures to determine which acute features are most predictive of functional outcome.

Ultimately, research derived from this study may be used in establishing new prognostic guidelines for patients with severe brain injury. Current prognostic tools have a primary utility of predicting poor neurologic outcome; however, even the most robust tools provide little insight into the chances of good recovery (46). Neuroimaging methods may be of use in this regard, as they can be used to map changes in the functional and structural integrity of the brain following injury and relate that directly to behavioral outcome. Indeed, a growing number of neuroimaging studies have demonstrated the positive prognostic potential of fMRI, but these results remain to be validated with a larger cohort of patients (17, 47–49). The pressing need for improved prognostic tools is further highlighted by the high variability in the withdrawal of life-sustaining measures across medical centers (50). These differences are guided by physician's perceptions of long-term prognosis (51), further emphasizing the need for accurate and objective prognostic markers. By revealing residual cognitive function in the midst of clinical uncertainty, functional neuroimaging may aid in the prognostic process and therefore affect the outcome of discussions regarding the continuation of care or the withdrawal of life-sustaining measures. The results of this study will not directly inform the prognosis or diagnosis of patients enrolled in study procedures, but rather, may inform future prognostic and diagnostic guidelines for including functional neuroimaging into the standard of care. Importantly, our local ethics research board has restricted the research team from sharing these results with the clinical team as this study is purely scientific and should not directly impact patient care.

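### AUC is the only stated yardstick for comparing imaging with traditional markers, so any comparator entered as present/absent should also be compared at its own operating point

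*Protocol article*

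**What the plan says.** The Statistical Analysis section of the protocol article sets up a head-to-head comparison: "Outcome predictors (as assessed by the area under a receiver operating characteristic curve) will be compared between acute neuroimaging findings and traditional prognostic markers". The comparators are given as examples: "such as EEG reactivity, pupillary reflexes, brainstem reflexes, serum biomarkers, evoked potential results". The purpose is "to assess whether functional neuroimaging responses are more accurate". No test, margin or decision rule is named for this comparison, and no scale is given for any of the traditional markers. The section on neurological examination and rating scales records "clinical EEG/evoked potential findings" without stating how they are coded.

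The main imaging predictors are graded. For the sensory tasks the analysis is the "rank correlation between the extent of acute sensory processing and a patient's behavioral scores"; for resting state the predictor is the "degree of acute functional connectivity, as measured by the correlation value to healthy controls"; the movie task uses a correlation with the control group.

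Sensitivity, specificity and predictive values are planned for the imaging procedures, and a ROC cut-off is sought for each paradigm. The article does not plan the same measures for the traditional markers, nor a comparison of the two at a common threshold. The Discussion adds: "Current prognostic tools have a primary utility of predicting poor neurologic outcome".

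**The concern.** AUC averages performance over all thresholds. A graded predictor earns credit at every one of them. A marker read only as present or absent supplies one ROC point joined to the corners by straight lines. When the two AUCs are subtracted, the difference mixes how well each marker separates the outcome groups with how many cut points its scale offers.

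The gap is largest when the present/absent marker sits at an extreme operating point. The Discussion's remark that current tools serve mainly to predict poor outcome makes such use plausible for some comparators, although the article does not say so of any particular marker.

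At stake is the conclusion that functional imaging is more accurate than current markers. The Discussion hopes that the results will inform prognostic guidelines, so a ranking that depends partly on scale could carry weight later.

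**Working it through.** The article states no AUC, AUC difference or power for this comparison, so there is no figure to reproduce. The check asks how large the effect of scale can be.

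**Inputs.** From the article: AUC as the yardstick, graded imaging predictors, and the list of comparators. Assumed: a normal, equal-variance marker distribution in each outcome group; an underlying AUC of 0.70 to 0.90; and a comparator entered as present/absent.

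**Formulae.** With group separation d, graded AUC = Φ(d/√2), so d = √2·Φ⁻¹(AUC). The same signal cut once has AUC = (sensitivity + specificity)/2. At the best cut this equals Φ(d/2). At 95% specificity, sensitivity = Φ(d − 1.645).

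**Worked case, underlying AUC 0.80.** d = 1.190.
- Best cut: Φ(0.595) = 0.724, a gap of 0.076.
- 95% specificity: sensitivity = Φ(−0.455) = 0.325, so AUC = (0.325 + 0.95)/2 = 0.637, a gap of 0.163.

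| Graded AUC | Best cut | Gap | 95% specificity | Gap |
|---|---|---|---|---|
| 0.70 | 0.645 | 0.055 | 0.567 | 0.133 |
| 0.75 | 0.683 | 0.067 | 0.597 | 0.153 |
| 0.80 | 0.724 | 0.076 | 0.637 | 0.163 |
| 0.85 | 0.768 | 0.082 | 0.689 | 0.161 |
| 0.90 | 0.818 | 0.082 | 0.758 | 0.142 |

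**A reversed ranking (illustrative values).** Suppose a traditional sign is abnormal in 30% of poor-outcome and 1% of good-outcome patients. Its AUC is (0.30 + 0.99)/2 = 0.645. Suppose imaging has AUC 0.75, so d = 0.954. By AUC, imaging leads.
- Predicting poor outcome at the sign's own 1% false-positive rate, imaging detects Φ(0.954 − 2.326) = 8.5% of poor outcomes, against 30%.
- Predicting good outcome, the sign's false-positive rate is 70% and its sensitivity 99%. Imaging at 70% has sensitivity Φ(0.954 + 0.524) = 93%.
- To equal the sign at the 1% point, imaging would need d = 2.326 − 0.524 = 1.802, an AUC of Φ(1.802/√2) = 0.90.

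**How often a test would pick this up.** Simulation, 1,000 runs per setting, paired DeLong test, two-sided 0.05. Assumed: 30% good outcome, correlation 0 or 0.5, underlying AUC 0.75 or 0.85 for both markers. With one marker cut at its best point, the graded one came out significantly better in 17% to 39% of runs at N = 100 and 41% to 88% at N = 350. With both on the same scale the rate was 2.2% to 3.5%. The contrast shows that scale drives the difference. The higher rates are not false-positive rates, because once one marker is cut the two AUCs truly differ.

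**The case against.** **Coding is not stated.** The article never says that pupillary reflexes, EEG reactivity or evoked potentials enter as present/absent, and coding may be set out in a fuller document. This stands: the absence of a scale is not itself a fault, and the point is conditional on the coding.

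**The contrast is not uniform.** Serum biomarkers are normally levels, and brainstem reflexes can be scored ordinally (the FOUR Score is collected). On the imaging side, fNIRS channels are classed as activated or not. A yes/no imaging result set against a biomarker level would be disadvantaged in the same way. This also stands and limits the scope.

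**A present/absent marker carries less information.** A reader might infer that graded imaging must win by format although the information is equal. The documents and the arithmetic do not support that. Equality holds only for the underlying signal before it is cut; what is lost by cutting is a real loss if the marker exists only in that form. A present/absent marker that is better by more than the gap still comes out ahead.

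**Covariates shrink the gap.** The plan will account for age, gender, days since injury, down time, MODS and SOFA. If these enter the ROC models, the marker no longer gives a single ROC point. For underlying AUC 0.80 and an assumed independent covariate score with AUC 0.60 to 0.80, the gap falls from 0.076 to about 0.02 to 0.05 at the best cut, and from 0.163 to about 0.04 to 0.11 at 95% specificity. The effect is reduced, not removed.

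**The study seeks markers of good recovery.** A comparison at a poor-outcome threshold may seem beside the point. But the ROC analysis covers both good and poor outcome, and the illustrative sign also leads in the good-outcome direction at its own operating point.

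**Conclusion.** The point holds in a limited form. AUC is the sole stated yardstick for the comparison with traditional markers. Where a graded imaging predictor meets a comparator entered as present/absent, the unadjusted AUC gap includes a part due to the number of thresholds: about 0.06 to 0.08 at the best cut and 0.13 to 0.16 at 95% specificity, for an underlying AUC of 0.70 to 0.90 under an equal-variance normal model. Covariate adjustment would make it smaller. AUC can also place imaging ahead while it performs worse where the traditional marker is used.

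This rests on the assumed present/absent coding. It does not apply to comparators used as levels or ordinal scores, or to yes/no imaging readouts. A reader might also infer that the plan will declare imaging superior on AUC; the text only sets out to assess the question and gives no decision rule. AUC comparison is a standard method and need not be dropped. What is missing from the stated method is a comparison at the operating point of the present/absent markers.

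**What to change.** In the Statistical Analysis section, keep the AUC comparison and add the following.

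1. For every comparator that enters as present/absent, read imaging sensitivity from its ROC curve at that marker's own false-positive rate. Report the paired difference in sensitivity with a bootstrap interval, both for predicting good and for predicting poor outcome.
2. Report sensitivity, specificity, PPV and NPV for the traditional markers as well as for imaging.
3. Rest any statement that imaging is more accurate than a present/absent marker on the matched comparison, with the AUC difference alongside.

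The cost is analysis wording only; no new data are needed. The downside is a wider interval at a single operating point than for an AUC, and probably a smaller claim for imaging.

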## Abstract

Multi-modal neuroimaging techniques have the potential to dramatically improve the diagnosis of the level consciousness and prognostication of neurological outcome for patients with severe brain injury in the intensive care unit (ICU). This protocol describes a study that will utilize functional Magnetic Resonance Imaging (fMRI), electroencephalography (EEG), and functional Near Infrared Spectroscopy (fNIRS) to measure and map the brain activity of acute critically ill patients. Our goal is to investigate whether these modalities can provide objective and quantifiable indicators of good neurological outcome and reliably detect conscious awareness. To this end, we will conduct a prospective longitudinal cohort study to validate the prognostic and diagnostic utility of neuroimaging techniques in the ICU. We will recruit 350 individuals from two ICUs over the course of 7 years. Participants will undergo fMRI, EEG, and fNIRS testing several times over the first 10 days of care to assess for residual cognitive function and evidence of covert awareness. Patients who regain behavioral awareness will be asked to complete web-based neurocognitive tests for 1 year, as well as return for follow up neuroimaging to determine which acute imaging features are most predictive of cognitive and functional recovery. Ultimately, multi-modal neuroimaging techniques may improve the clinical assessments of patients' level of consciousness, aid in the prediction of outcome, and facilitate efforts to find interventional methods that improve recovery and quality of life.

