To establish whether fMRI measures of covert awareness can be used in the diagnosis of acute disorders of consciousness in the ICU, we will seek to ascertain the proportion of patients who show signs of covert awareness, in the form of plot and command following, and subsequently the proportion of those participants who can use mental imagery tasks as a means of communication. A variety of statistical measures will be used, where appropriate, to determine whether neural activity differs between prognostic groups (i.e., survivors vs. non survivors; good outcome vs. poor outcome). Machine learning models will also be applied to evaluate neuroimaging measures as predictors of covert consciousness and subsequent recovery. Features will be extracted from each imaging modality and a two-class linear classifier (such as support vector machines) will be used to classify patients as survivors and non survivors. Patient outcome 12-months post injury will be used as ground truth while training the classifier. Features such as the median change in the signal during the task period and the correlation coefficient between the time series and the theoretical activation model (i.e., box function convolved with a hemodynamic response) will be extracted from the time courses obtained from task-based stimuli. For the resting state task, previous work has shown that the frontoparietal network and the default mode network are critical for consciousness, therefore, the strength of the correlation between channels in these networks will be used to supplement the features extracted from the active tasks. In addition to supervised machine learning, the feasibility of deep learning to predict outcome will also be assessed. The main advantage of deep learning is the ability to extract features that could be overlooked by the user. Given the breadth of data, deep learning approaches such as the convolutional, feedforward, and artificial neural network may be beneficial (45). These options will be further explored once enough data is collected to make this type of analysis feasible. Finally, a feature ranking approach may be used to quantify the importance of each method and metric.

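### The supervised classifier is meant to predict recovery but is trained to separate survivors from non-survivors, so poor-outcome survivors share a class with good recoveries

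*Protocol article*

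**What the plan says.** The Abstract of the protocol article states the goal as finding "objective and quantifiable indicators of good neurological outcome and reliably detect conscious awareness". The Discussion repeats the aim of identifying markers of good recovery and notes that existing tools mainly predict poor outcome.

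The Statistical Analysis section introduces the modelling step as follows: "Machine learning models will also be applied to evaluate neuroimaging measures as predictors of covert consciousness and subsequent recovery". It then names the classes: "a two-class linear classifier (such as support vector machines) will be used to classify patients as survivors and non survivors". The next sentence adds: "Patient outcome 12-months post injury will be used as ground truth while training the classifier". That sentence fixes the time point but names no scale and no cut.

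Earlier in the same section, a good outcome is described as "a recovery that allows for sufficient function for independent activities of daily life". Poor outcome covers severe disability affecting every part of daily living, coma, vegetative state and death. On the GOS-E, good is set at "a score of 4 or greater, signifying the ability to be left alone for up to 8 h during the day without assistance".

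The Discussion acknowledges that deaths after withdrawal of life-sustaining measures confound estimates of accuracy. It states an aim to group them apart from natural deaths when judging which imaging markers best predict recovery.

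**The concern.** The stated purpose of the classifier and its named classes do not match. The purpose is recovery; the classes are alive and dead. Under the section's own definition of poor outcome, a patient alive at 12 months in a vegetative state is a poor outcome, but under the survival label that patient is in the same class as someone living independently.

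A model trained this way looks for features that separate the living from the dead. Nothing in its training separates good recovery from dependent survival, which is the distinction that the Abstract and Discussion say is missing from current practice. Its accuracy, or a feature ranking drawn from it, could be reported as evidence about recovery when the label does not support that.

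The second, smaller concern is the definition of good outcome. Independence in daily life and being safe alone for part of the day are not the same standard. ROC results at the GOS-E cut could be read as accuracy for independence.

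**Working it through.** **1. Comparing the labels.** The plan states no accuracy, power or sample-size figure that depends on the label (the Feasibility section sets 350 on feasibility grounds), so there is no figure to reproduce. The two labels treat 12-month states as follows:

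| State at 12 months | Good/poor label | Survival label |
|---|---|---|
| Good outcome | good | survivor |
| Severe disability in all aspects of daily living, coma or vegetative state | poor | **survivor** |
| Death | poor | non-survivor |

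The labels disagree on the middle row only, which is the row a prognostic model for good recovery has to separate from the first.

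**2. How many patients fall in that row.** The documents give neither a mortality rate *m* nor a good-outcome rate *g*, both as shares of the cohort. I assume *m* = 0.35–0.50 and *g* = 0.20–0.40, with all 350 patients contributing. Poor-outcome survivors = 350 × (1 − *m* − *g*).

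- Smallest: 350 × (1 − 0.50 − 0.40) = 35 (10%).
- Largest: 350 × (1 − 0.35 − 0.20) = 157.5, about 158 (45%).
- Middle case, *m* = 0.40 and *g* = 0.30: 350 × 0.30 = 105 (30%).

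**3. What a perfect survival classifier would achieve for good outcome.** Suppose it separated survivors from non-survivors without error and its output were read as a prediction of good outcome. Sensitivity is 1. The other measures are:

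- PPV = *g* / (1 − *m*)
- specificity = *m* / (1 − *g*), that is, deaths over all poor outcomes
- AUC = (1 + specificity) / 2

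In the middle case there are 140 deaths, 105 good outcomes and 105 poor-outcome survivors. PPV = 105/210 = 0.50, specificity = 140/245 = 0.57 and AUC = 0.79. Over the assumed ranges:

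- PPV runs from 0.20/0.65 = 0.31 to 0.40/0.50 = 0.80.
- Specificity runs from 0.35/0.80 = 0.44 to 0.50/0.60 = 0.83.
- AUC runs from 0.72 to 0.92.

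These figures illustrate the mismatch; they do not forecast this study's results.

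**4. Deaths after withdrawal.** Both labels put these deaths in the unfavourable class, so changing to good/poor corrects the middle row of the table but not this problem. The separate grouping intended in the Discussion has no counterpart in the two-class description.

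**5. The GOS-E cut.** The verbal definition of good requires independence, while the gloss on a score of 4 requires only being left alone for up to 8 hours. A patient at exactly 4 is not shown to be independent, and is not plainly disabled in every part of daily living either. The document gives no share of patients expected at that score, so this point cannot be sized.

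**The case against.** The strongest reply is that survival is not the study's main label. The prognostic objective is analysed by Spearman correlation with the GOS-E at 3, 6 and 12 months (12 months primary), and by ROC curves for good versus poor outcome. Group comparisons use both splits. The survivor label belongs to a supplementary modelling step. This stands: a reader might infer that the whole plan measures the wrong outcome, and the document does not support that.

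A second reply is that the sentence on 12-month ground truth may already point to the GOS-E. It may, but it names no scale or cut and does not displace the two classes named just before it. A fuller plan might settle the matter, but the article does not leave the classes open.

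A third reply is that GOS-E 4 or above is the protocol's explicit definition of good, with a cited source. This also stands. A reader might conclude that the cut is wrong, but the document does not reproduce the GOS-E categories, and the cut is compatible with its description of poor outcome. Only the disagreement between wording and cut is established.

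Finally, a reader might combine the survival label with the Discussion's figure of about 70% of deaths following withdrawal and say that the model would simply learn who was kept on support. That figure comes from a cited study of ICU deaths, not from this cohort or from deaths to 12 months. The confounding is real and the protocol acknowledges it, but its size here is unknown.

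**Conclusion.** The point holds for the supervised classifier. As written, its label puts patients the protocol calls poor outcomes in the same class as good recoveries, so its results cannot be presented as identifying markers of good recovery. The other prognostic analyses are not affected by the survival label, apart from the survival half of the group comparisons, which has a good/poor comparison beside it.

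The number of patients affected cannot be derived from the documents. The range of about 10–45% of the cohort rests entirely on the assumed mortality and good-outcome rates and on all 350 patients contributing, although the Feasibility section expects some data loss and withdrawal. The conclusion does not depend on where in that range the truth lies, because the conflict is between the named classes and the stated purpose.

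The disagreement between the independence wording and the GOS-E cut is secondary. It needs reconciling and does not show that the cut is wrong.

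**What to change.** **Classifier label.** In the Statistical Analysis section, make the 12-month GOS-E good/poor outcome the classifier's main label, with 12-month survival as a secondary label. State the scale and cut in the sentence on ground truth. The GOS-E is already collected at 12 months, so this costs a change of wording made before training.

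**Deaths after withdrawal of life-sustaining measures.** Good/poor still counts these deaths as poor, so the separate grouping in the Discussion should be carried into the classifier, for example with a sensitivity analysis that excludes them. The cost is a smaller training set in that analysis. It would show how far the result depends on these deaths but cannot recover what their outcome would have been.

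**Good-outcome definition.** Make the verbal definition and the GOS-E cut agree, and report the ROC results at the next higher cut as a sensitivity analysis. The cost is one repeat of each ROC table, with fewer patients in the good class and so wider intervals.

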#### FMRI Data Analysis

fMRI data will be preprocessed and analyzed using Statistical Parametric Mapping (SPM) (http://www.fil.ion.ucl.ac.uk/spm). For the passive paradigms (somatosensory and auditory) as well as the command follow tasks, the analyses will be based on the general linear model (GLM) using the canonical hemodynamic response function. A GLM will be created with regressors for each condition in each active or passive paradigm. Six individual motion parameters will be included as covariates to account for variations due to movement. Healthy control data will be used to generate regions of interest (ROI) masks using a threshold of *p* <0.05, family-wise error corrected. The ROIs will be created using the SPM compatible MarsBaR software (http://marsbar.sourceforge.net/). The statistical threshold to detect neural activity may vary based on the task with supporting evidence from previous literature (10, 11). To assess resting-state functional connectivity, an independent component analysis will be used to decompose the resting state BOLD signal into 20 statistically independent spatial and temporal components with the GIFT software package (http://icatb.sourceforge.net). Components will then be spatially correlated to 10 resting state network templates derived from the BrainMap database (39).

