#### FNIRS Data Analysis

The data will be preprocessed and analyzed using MATLAB and freely available software packages such as NIRS Toolbox and Homer2. Each time series will be filtered to eliminate the effects of physiological changes such as heart rate and breathing, corrected for motion artifacts and short-channels will be regressed from the longer channels to reduce scalp contributions (42). For the sensory processing and command following tasks, the time courses will be fitted to the general linear model to detect significant hemoglobin changes. A channel will be considered activated if there is a significant increase in oxyhemoglobin and a concurrent significant decrease in deoxyhemoglobin. Network analysis will be performed for the resting state analysis (43). Pearson correlation coefficient (*r*) between the time-courses of two channels for all possible combinations will be computed, and these will be considered linked if the *r* is above a predetermined threshold. Graph theory will also be used to extract global network parameters to characterize the network.

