Given that fMRI and fNIRS rely on BOLD imaging principles, we will examine fNIRS results against fMRI findings to assess the accuracy of fNIRS to detect brain activity during various tasks at the bedside. For the tasked based paradigms, ROI will be identified from the fMRI results and the fNIRS channels corresponding to those areas to determine the presence of significant changes in oxy- and deoxyhemoglobin. For the resting state task, the strength of the correlation across functional networks of interest (i.e., frontoparietal network, default mode network) will be compared (15, 17). Furthermore, given that two MRI scanners with different field strengths will be used in this protocol, we will analyze data on the 3T and 1.5T as separate cohorts of patients based on which MRI scanner the data was obtained from. We also plan to address how this will impact the data by running research scans on both scanners in the same group of healthy volunteers. Finally, investigators will be blinded when analyzing predictive data and the study coordinator will be blinded from the acute imaging results when collecting outcome measures.

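### For task paradigms, fNIRS accuracy is checked only in channels over fMRI-identified areas, so it can show co-detection with fMRI but not spatial specificity

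*Protocol article*

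**What the plan says.** The last part of Statistical Analysis gives the purpose of the comparison: "we will examine fNIRS results against fMRI findings to assess the accuracy of fNIRS to detect brain activity during various tasks at the bedside". In the task paradigms, the method is that "ROI will be identified from the fMRI results and the fNIRS channels corresponding to those areas to determine the presence of significant changes", meaning both hemoglobin signals. No channels outside those areas are mentioned, and nothing is said about patients in whom fMRI shows no response.

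Four other statements bear on the point:

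- FNIRS Data Analysis defines an active channel: "A channel will be considered activated if there is a significant increase in oxyhemoglobin and a concurrent significant decrease in deoxyhemoglobin".
- FMRI Data Analysis describes one way of making regions: "Healthy control data will be used to generate regions of interest (ROI) masks". The fNIRS comparison does not say whether these masks are the regions it means.
- Earlier in Statistical Analysis, at the end of the paragraph relating imaging to long-term outcome: "We will also determine the sensitivity, specificity, positive predictive value, and negative predictive value for the imaging procedures outlined in the protocol".
- Resting state is compared differently: "For the resting state task, the strength of the correlation across functional networks of interest" is set against its fMRI counterpart. The point below does not concern it.

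**The concern.** Accuracy against a reference has two sides: responding where the reference is positive, and staying silent where it is negative. The rule for the task paradigms goes to the places fMRI points to and asks whether fNIRS responds there. That covers the first side only.

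At stake is the objective in the Introduction of developing bedside methods and establishing whether they can supplement diagnosis and prognostication. If fNIRS responds in most fMRI-identified regions, that may mean it follows regional cortical activity. It may also mean that it responds widely across the head. The stated comparison gives the same result in both cases, so a favourable finding would support less than the word accuracy suggests.

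**Working it through.** The article states no figure for fNIRS accuracy, so there is none to reproduce. The check applies the stated rule to simple signals.

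**Step 1. Which cells are filled.** Classify each channel by fMRI (active or inactive at that place) and by fNIRS (active or inactive):

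- a = both active; c = fMRI active, fNIRS inactive
- b = fMRI inactive, fNIRS active; d = both inactive
- sensitivity = a/(a + c); specificity = d/(b + d)

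If the regions are where fMRI is active, the rule fills a and c only. Then b + d = 0, so specificity is 0/0 and cannot be estimated.

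**Step 2. Two signals the rule cannot separate.** Let q be the share of channels over fMRI-active areas. The article does not give q; I assume 0.1 to 0.5. Both signals are taken to satisfy the FNIRS Data Analysis activation rule wherever they are active.

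| | Active in every channel | Active in exactly the fMRI-active channels |
|---|---|---|
| Region channels only, a/(a + c) | q/q = 100% | q/q = 100% |
| All channels, sensitivity | 100% | 100% |
| All channels, specificity | 0/(1 − q) = 0% | (1 − q)/(1 − q) = 100% |
| All channels, proportion correct | q = 10% to 50% | 100% |
| Youden index (sensitivity + specificity − 1) | 0 | 1 |

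The first row is all that the stated rule examines, and it is the same for both signals.

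**Step 3. Which patients enter.** Let p be the share of patients whose fMRI is positive on a task. It is not given for this comparison; I assume 15% to 70%.

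- *Regions from each patient's own activation.* A patient with no fMRI response has no region and is not scored. An fNIRS signal that is always active co-detects in every scored patient, and no false positive can appear at patient level either.
- *Regions from the healthy-control masks.* Every patient has the same channels scored. The always-active signal agrees with fMRI in a share p of patients (15% to 70%) and disagrees in 1 − p (85% to 30%); patient-level specificity is 0%. False positives by patient become visible if results are cross-classified. Channels outside the masks are still unused, so spatial specificity remains untested.

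The two readings therefore differ on patient-level specificity, and neither provides spatial specificity.

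**The case against.** The case on the other side has real content.

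- *Condensed article.* An article may leave the agreement statistic, the cross-table and the intervals to a fuller document. I accept that, and do not count the missing formula as a fault. What the article does state, however, is which channels are examined, and that is what limits the comparison.
- *Control masks.* The only region-making procedure described uses healthy controls. If those are meant, fMRI-negative patients are scored. A reader might infer that an fNIRS signal active everywhere would be declared fully accurate; the article does not support that, because it defines no accuracy score and the control-mask reading would expose disagreement by patient. The loss of spatial specificity stands either way.
- *Direction of change.* The comparison speaks only of significant changes, and a reader might infer that a shift of both signals in the same direction would count as agreement. FNIRS Data Analysis already requires a rise in oxyhemoglobin with a fall in deoxyhemoglobin, and nothing in the comparison revokes it. That inference fails.
- *Preprocessing.* Physiological filtering, motion correction and short-channel regression reduce signals that could mimic activation. They do not measure how often false activation remains.
- *Promised specificity.* The general promise covers the imaging procedures, so it could be read to include fNIRS. It sits in the paragraph on outcome and is not tied to fMRI as reference. The task rule names no fMRI-negative units from which specificity could be calculated.
- *Communication.* A reader might infer that bedside communication rests on this comparison. The Covert Awareness Paradigm section instead makes it depend on the patient's own reliable command-following activity, and analyses subjective answers only if verifiable questions are answered correctly. That inference also fails.

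**Conclusion.** The concern holds in limited form, for the task paradigms only. As written, the comparison estimates co-detection with fMRI and cannot estimate spatial specificity. Whether it can show false positives at patient level depends on which regions are meant, and the article leaves that open.

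The structural conclusion needs no numerical assumption beyond taking the stated rule at its word. The ranges do: 10% to 50% rests on the assumed share of channels over fMRI-active areas, and 15% to 70% on the assumed share of fMRI-positive patients. They show how far apart co-detection and proportion correct can lie for an extreme signal; they do not predict this study's result. The outcome analyses based on the GOS-E are unaffected. It is a change worth making before the fNIRS and fMRI data are compared.

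**What to change.** Reword the task-paradigm comparison in Statistical Analysis as follows:

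1. Use the healthy-control masks from FMRI Data Analysis, and the fNIRS channels over them, in every patient with both tests, whatever that patient's fMRI shows.
2. Call a channel active by the rule in FNIRS Data Analysis: oxyhemoglobin up and deoxyhemoglobin down, both significant.
3. For each task, cross-classify fMRI response present or absent against fNIRS response present or absent.
4. Report sensitivity and specificity with confidence intervals, naming fMRI as the reference.
5. Report the activation rate in channels outside the masks as a negative control. A patient's fMRI may itself be active outside the control mask, so read this rate beside the fMRI result at the same place.

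No new testing is needed. Figure 1 places fMRI and fNIRS together in the days 4–6 window, and FNIRS Procedures describes a montage from frontal to parietal areas, so channels outside a given task's region should already be recorded. The cost is a little more analysis and possibly a less favourable accuracy figure. Because the 1.5T and 3T data are to be analysed as separate cohorts, the tables will be smaller and the intervals wider.
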